# Phase 2 randomized placebo controlled double blind study to assess the efficacy and safety of tecfidera in patients with amyotrophic lateral sclerosis (TEALS Study)

**DOI:** 10.1097/MD.0000000000018904

**Published:** 2020-02-07

**Keywords:** ALS, ASLFRS-R, neuroimmunity, TECFIDERA, Treg

## Abstract

**Background::**

Amyotrophic lateral sclerosis (ALS) is a progressive and fatal neurodegenerative disorder of the human motor system. Neuroinflammation appears to be an important modulator of disease progression in ALS. Specifically, reduction of regulatory T cell (Treg) levels, along with an increase in pro-inflammatory effector T cells, macrophage activation and upregulation of co-stimulatory pathways have all been associated with a rapid disease course in ALS. Autologous infusion of expanded Tregs into sporadic ALS patients, resulted in greater suppressive function, slowing of disease progression and stabilization of respiratory function. Tecfidera (dimethyl fumarate) increases the ratio of anti-inflammatory (Treg) to proinflammatory T-cells in patients with relapsing remitting multiple sclerosis and rebalances the regulatory: inflammatory axis towards a neuroprotective phenotype. Consequently, the aim of this study was to assess the efficacy, safety, and tolerability of Tecfidera in sporadic ALS.

**Methods::**

The study is an investigator led Phase 2 multi-center, randomized, placebo controlled, double blind clinical trial assessing the efficacy and safety of Tecfidera in patients with sporadic ALS. The study duration is 40 weeks, with a 36-week study period and end of study visit occurring at 40 weeks or at early termination/withdrawal from study. The TEALS study has been registered with the Australian and New Zealand Clinical Trials registry (ANZCTR) under the trials registration number ACTRN12618000534280 and has been approved by the Human Research Ethics Committee and Research Governance Office at the lead site (Westmead Hospital) with the ethics number HREC/17/WMEAD/353. The participating sites have obtained site specific ethics and governance approvals from the local institution.

**Results::**

The primary endpoint is slowing of disease progression as reflected by the differences in the ALS Functional Rating Score-Revised (ALSFRS-R) score at Week 36. The secondary endpoints will include effects in survival, lower motor neuron function, respiratory function, quality of life and safety.

**Conclusion::**

This Phase 2 multi-center, randomized, placebo controlled, double blind clinical trial will provide evidence of efficacy and safety of Tecfidera in sporadic ALS.

## Introduction

1

Amyotrophic lateral sclerosis (ALS) is a progressive and fatal neurodegenerative disorder of the human motor system, with median survival of 3 to 5 years.^[1,2]^ The currently licensed treatments for ALS include riluzole [anti-glutamatergic agent]^[3–5]^ and edaravone,^[6]^ both of which provide limited benefits. The etiology of sporadic ALS remains unresolved, although a complex multistep interaction between genetic and molecular processes, along with environmental influences, seems likely.^[2,7,8]^ Over the past several decades there have been more than 250 separate clinical studies searching for an effective treatment for ALS, none of which were successful in slowing the progression of ALS.^[9,10]^

There is accumulating evidence for a role of neuroinflammation in ALS pathogenesis, with astrocytes, microglia and T cells actively contributing to neurodegeneration and disease progression in ALS.^[11–16]^ Specifically, reduced expression of mutant superoxide dismutase one (SOD1) protein in microglia^[17]^ and astrocytes^[18]^ has been associated with a slower rate of disease progression. In addition, elimination of functional CD4^+^ T cells accelerates the rate of disease progression in SOD1 mouse models, a process that can be rectified by reconstitution of the immune system through bone marrow transplantation.^[12,19]^

Importantly, upregulation of regulatory T cells (CD4^+^FoxP3^+^ Tregs) in blood and lymph node tissue was reported in the early disease stages of the SOD1 mouse model, with increased expression of FoxP3 mRNA, a key transcriptional regulator of Tregs, evident in the spinal cord.^[20]^ In addition, upregulation of anti-inflammatory cytokines (interleukin [IL]-4, IL-10) is also evident in the early stages of disease resulting in a neuroprotective microglia (M2) phenotype which provides neurotrophic support.^[13]^ With disease progression, there is upregulation of proinflammatory cytokines IL-1β, IL-6 and interferon-γ [IFN-γ]) along with expansion of the CD4^+^CD25^−^ T effector levels, decline in Treg and transition of the microglia to a neurotoxic M1 phenotype.^[13]^ Interestingly, adoptive transfer of Tregs into SOD1 mouse models induces the M2 phenotype and prolongs survival,^[13,21]^ thereby suggesting that Tregs may be neuroprotective in ALS by modulating microglial activation. Of further relevance, expansions of the effector population in the SOD-1 mouse model by IL2 treatment was associated with reduced disease progression, prolonged survival and preservation of motor neuron size and dendritic networks,^[22]^ underscoring a potential therapeutic effect of an immune modulating approach.

Neuroinflammation also appears to be a key modulator of disease progression in ALS patients.^[15,22]^ A reduction of Treg levels, along with an increase in pro-inflammatory effector T cells, increased macrophage activation and upregulation of co-stimulatory pathways have been associated with a rapid disease course in ALS patients.^[23–28]^ Of relevance, rapidly progressive ALS patients express a reduced level of FoxP3 mRNA in the spinal cord along with an increase in peripheral monocytes expressing pro-inflammatory genes.^[15,29]^ Taken together, these findings suggest that the immune balance is skewed to a more proinflammatory state in ALS patients with a rapidly progressive disease course. Importantly, autologous infusion of expanded Tregs into sporadic ALS patients, resulted in greater suppressive function, slowing of disease progression and stabilization of respiratory function,^[30]^ underscoring the therapeutic potential of the Treg based neuromodulatory approach in ALS.

Enhancement of Treg levels in humans can be achieved safely and effectively by using dimethyl fumarate (tecfidera), a commercially available medication for treatment of the relapsing-remitting form of multiple sclerosis.^[31,32]^ In relapsing remitting multiple sclerosis patients, tecfidera was shown to increase the ratio of anti-inflammatory to proinflammatory T-cell subsets.^[33,34]^ Tecfidera also results in stabilization of Treg frequency and a concomitant reduction in pro-inflammatory T-cells [CD4+ INFγ+; CD8+ INFγ+],^[33]^ underscoring its potency in rebalancing the regulatory: inflammatory axis towards a neuroprotective phenotype. Consequently, the aim of the current Phase II randomized placebo controlled multicenter trial was to assess the efficacy and safety of tecfidera in sporadic ALS. Current manuscript publishes the trial protocol (version 3.0) which has been approved by the ethics committee.

## Methods

2

### Aims and objectives

2.1

The primary aim of this clinical trial as to assess the efficacy of tecfidera (dimethyl fumarate, DMF) on disease progression in sporadic ALS patients. The secondary aim of this study is to assess effects of tecfidera in sporadic ALS patients on survival, lower motor neuron dysfunction, respiratory dysfunction, quality of life as well as safety and tolerability. The primary and secondary aims of this will be achieved through a multi-center, randomized, double-blind, placebo controlled clinical trial conducted on sporadic ALS patients that will be prospectively recruited from 6 ALS centers in Australia. The total study duration will be 40 weeks, with a 36-week study period and an end of study visit occurring at 40 weeks or at early termination/withdrawal from study.

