### Secondary outcome measures

2.3

The secondary outcome measures will be measured at screening, baseline, week 12, 24, 36 and 40. The secondary endpoints will include measures of efficacy and safety.

1.SurvivalSurvival will be defined from symptom onset to death of patients or tracheostomy insertion, whichever occurs first and will be measured in months.2.Lower motor neuron functionLower motor neuron function will be assessed by clinical and neurophysiological biomarkers and will included muscle strength and motor amplitudes.**-Muscle strength**(a) *Medical Research Council score*: Clinical assessment of muscle strength will be made by the Medical Research Council (MRC) score. The MRC score is a standard clinical score used in clinical practice and will be performed by the neurologist at each site. This score assesses muscle strength on a 5-point score as follows:5 = Normal strength.4 = Active movement against gravity and resistance.3 = Weak contraction against gravity.2 = Active movement with gravity eliminated.1 = Minimal contraction.0 = Complete paralysis.The following movements will be assessed in each patient:*-Upper limbs*: Shoulder abduction, elbow flexion, elbow extension, wrist extension, finger extension, finger abduction, and thumb abduction on both sides. The total score when strength normal in the upper limbs will be 70.*-Lower limbs*: Hip flexion, abduction, adduction and extension, knee flexion and extension, and ankle dorsiflexion and plantarflexion. The total score when strength is normal in the lower limbs will be 80. The upper and lower limb MRC scores will be combined yielding a maximum score of 150 (0 severe weakness to 150 normal strength).(b) *Hand dynamometry*: Muscle strength will also be assessed by hand-held dynamometry (JAMAR PLUS, Patterson Medical, Warrenville, IL). A spring-loaded device that “breaks” at pre-set forces will be used to assess readings obtained by hand-held dynamometry throughout the study. Wherever possible, the same rater will be used at each site for each assessment. Grip strength dynamometry for both hands will be acquired, and the mean force in kilograms will be calculated. Measures will be obtained from each hand in triplicate-*Neurophysiological testing:* The degree of lower motor neuron loss will be determined neurophysiological testing performed on nerve conduction study machines (Nicolet EDX, System, Natus, Middleton, WI). The following parameters will be recorded from the intrinsic hand muscles on both sides.(a) *Neurophysiological Index (NPI)*: This is an established measure of lower motor neuron dysfunction in ALS.^[36]^ The NPI will be calculated from by stimulating the median nerve at the wrist and recording the motor response from the abductor pollicis brevis muscle using the following formula: 

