After completing Week 36 procedures, all patients will return to the study site at Week 40 for the End of Study Visit (4 weeks after the end of treatment visit). Patients who discontinue the study early will be asked to return to the study site for the early termination procedures 4 weeks after their last dose of Tecfidera/placebo. At this visit, neurological and physical examination will be performed and vital signs (blood pressure, pulse, temperature, and respiratory rate) will be recorded. The visit will also involve an assessment of ALSFRS-R, NPI and SI, FVC as measured by handheld spirometer, SNIP test, quantitative hand muscle testing by dynamometry, and global strength using MRC score. All patients will undergo laboratory evaluation of hematological and biochemical parameters as well as urinalysis. Urine will also be collected to test neurotrophin receptor P75 levels (secondary endpoint). An ALSSQOL-R questionnaire will also be completed by all patients. Adverse events and changes to concomitant medications will be observed and evaluated.

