## Trial status

6

The TEALS study commenced in October 2017 and is ongoing. We anticipate that the results will be available in the last quarter of 2020 or first quarter of 2021.

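### Survival is a secondary aim, but its collection is described only to Week 40, and less in early stoppers; a cheap status check would improve precision and reduce bias without making survival adequately powered

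*Protocol article*

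**What the plan says.** Section 2.1 of the protocol article sets a secondary aim to "assess effects of tecfidera in sporadic ALS patients on survival", among other outcomes. It then fixes the length of observation: "The total study duration will be 40 weeks, with a 36-week study period and an end of study visit occurring at 40 weeks".

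Section 2.3 lists survival first among the secondary outcomes. It "will be defined from symptom onset to death of patients or tracheostomy insertion, whichever occurs first", and is expressed in months. The same section gives the measurement times: "The secondary outcome measures will be measured at screening, baseline, week 12, 24, 36 and 40".

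For patients who discontinue, Section 3.4 asks for "early termination procedures 4 weeks after their last dose of Tecfidera/placebo", and Section 3.5 repeats this timing. The article describes no later check of vital status and no common closing date. Section 3.6 evaluates secondary efficacy in the intent-to-treat population, defined there as all randomised patients.

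Two other statements bear on the point. The Introduction describes ALS as a disease "with median survival of 3 to 5 years", without giving a time origin. Section 6 says "The TEALS study commenced in October 2017 and is ongoing", with results expected in the last quarter of 2020 or the first quarter of 2021.

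**The concern.** A window of about 9 months is short against a median of 36 to 60 months, so few events can be expected. A non-significant comparison on few events could be read as an answer to a named aim when the data are compatible with large benefit and large harm.

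The second issue is bias. The intent-to-treat population contains everyone randomised, but the described collection for an early stopper ends 4 weeks after the last dose. Section 3.5 requires withdrawal for drug-related Grade 4 events, persistent lymphopenia and liver enzyme rises, among other reasons. Such withdrawals could be more common on active treatment, so the missing follow-up may differ by arm and may be related to prognosis. The sample size allows for 20% dropout, which is 0.20 × 90 = 18 patients.

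**Working it through.** **The plan's own figure.** None is given for survival: no event count, effect or power. The 90 patients (60:30) in Section 2.4 were sized on ALSFRS-R and are taken as given here.

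**Inputs.** From the article: N = 90, 2:1 allocation, 40 weeks (40 × 7 / 30.4 ≈ 9.2 months), median survival 36 to 60 months, two-sided 5% level. Assumed: the median applies from randomisation, the hazard is constant, and (for the extended follow-up) accrual is uniform over 12 to 24 months. Accrual length is not stated. An accrual of 24 months plus 9.2 months is 33.2 months, which fits between October 2017 and October 2020 (36 months).

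**Formulas.**
- Events E = 90 × mean of [1 − exp(−ln 2 × t / median)] over the follow-up times t, under no treatment effect
- SE(log HR) = 1 / √(E × 2/9), since 2/3 × 1/3 = 2/9
- 95% CI factor each way = exp(1.96 × SE)
- Hazard ratio detectable with 80% power = exp(−2.80 × SE)

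**Week 40, worked for each median.**
- 60 months: E = 90 × [1 − exp(−0.693 × 9.2/60)] = 9.1; SE = 1/√2.02 = 0.70; CI factor 4.0; detectable HR 0.14.
- 36 months: E = 90 × [1 − exp(−0.693 × 9.2/36)] = 14.6; SE = 1/√3.24 = 0.56; CI factor 3.0; detectable HR 0.21.

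An estimate of exactly 1 would therefore have an interval of about 0.25 to 4.0 (9 events) or 0.33 to 3.0 (15 events).

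**Sensitivity at Week 40.** With 20% dropout, events fall to 8.1 (60 months) and 13.0 (36 months). With an assumed residual median of 24 or 18 months from randomisation, events rise to 21.0 or 26.8 and the CI factor falls to about 2.5 or 2.2. The overall range is about 8 to 27 events.

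**Follow-up to a common closing date, the last patient's Week 40.**

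| Follow-up | Events (median 60 / 36 months) | Ratio to Week 40 | CI factor | HR for 80% power |
|---|---|---|---|---|
| Week 40 only | 9.1 / 14.6 | 1 | 4.0 / 3.0 | 0.14 / 0.21 |
| 12-month accrual | 14.4 / 22.7 | 1.6 / 1.6 | 3.0 / 2.4 | 0.21 / 0.29 |
| 24-month accrual | 19.3 / 29.6 | 2.1 / 2.0 | 2.6 / 2.1 | 0.26 / 0.34 |

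**Power for a true hazard ratio of 0.5.** Events are fewer because the active arm has half the hazard. For medians of 60 and 36 months:
- Week 40: 6.1 and 10.0 events, power 12% and 18%
- 12-month accrual: 9.8 and 15.7 events, power 17% and 25%
- 24-month accrual: 13.3 and 20.8 events, power 22% and 32%

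At 2:1 allocation, 80% power for this effect needs 74 events. These figures assume the hazard ratio stays constant after treatment ends, so the two extended cases are optimistic.

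**The case against.** Low power for a secondary survival endpoint is ordinary in a 90-patient Phase 2 trial. The article claims no power for survival, and Section 3.6 already commits to 95% intervals beside estimates, so the imprecision would be visible. A fixed observation period is a legitimate design. Nearly all the added follow-up is off study drug, because the end-of-treatment visit is at Week 36, and the Introduction calls the drug commercially available, so later use outside the trial is possible. This all stands, and it limits the point to a cheap improvement.

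The event count also rests on an unstated origin. If "median survival of 3 to 5 years" runs from symptom onset, as the trial's own survival definition does, residual survival at randomisation is shorter and Week 40 would yield more events. That stands too. It is why 9 to 15 is conditional on an assumption, with 8 to 27 as the wider range.

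The objection does not answer the gap in early stoppers. Intervals show random error; they do not show bias from events that were never recorded.

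A reader might go further and infer that the trial cannot address survival as designed and that longer follow-up would cure this. The documents support neither half. An estimate with an interval can be produced at Week 40, and the extended analysis would still be well short of 74 events.

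**Conclusion.** The point holds as a specific, inexpensive improvement. As described, survival is observed to Week 40 at most and for less time in early stoppers, while the analysis population is everyone randomised. At 9 to 15 events the hazard ratio is known only to within a factor of 3 to 4 each way.

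A common closing date would bring the factor to 2.4 to 3.0 (12-month accrual) or 2.1 to 2.6 (24-month accrual). The more secure gain is complete status through Week 40, which depends on no accrual assumption and reduces the risk of censoring that differs by arm. The size and direction of that bias cannot be computed from the article.

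The figures rest on constant hazard, the median applied from randomisation, uniform accrual of assumed length and, for power, a constant hazard ratio. It would be tempting to say that the Week 40 event count follows from the protocol's own figures, or that the extension doubles the events. The first needs the time origin, which is not given; the second holds only near 24-month accrual. If the full protocol already includes a later status check that the article leaves out, that part of the point falls away.

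**What to change.** In Sections 2.3 and 3.4:

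1. Collect the status and date of death or tracheostomy for every randomised patient, including those who stop early, through Week 40 as a minimum and subject to consent. A telephone call or clinic record suffices.
2. Add one status check at a common closing date, the last patient's Week 40 visit.
3. Analyse by randomised arm with time counted from randomisation. The stated origin at symptom onset adds a period in which no enrolled patient could have had the event.
4. Keep the Week 40 analysis beside the close-out analysis, and report survival as an estimate with its interval and no efficacy conclusion.

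**Cost.** One extra status check per patient at study close, plus the Week 40 check in early stoppers, by existing site staff, with an ethics amendment and consent wording. Patients who have already finished or withdrawn may need renewed consent, and some may decline. Follow-up after Week 36 is off study drug and may dilute an effect, which is the reason for keeping both analyses.

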### Primary outcome measure

2.2

The primary outcome measure is slowing of disease progression as reflected by the differences in the ALS Functional Rating Score-Revised (ALSFRS-R) score at Week 36 between active and placebo groups. The ALSFRS-R is a validated rating instrument for monitoring the progression of disability in patients with ALS and is utilized for monitoring functional change in ALS patients. The score assesses various 4 domains including:

(i)bulbar function (speech, salivation, swallowing);(ii)fine motor task (handwriting, cutting food and handling utensils, with or without gastrostomy, dressing and hygiene);(iii)gross motor task (turning in bed, walking, climbing stairs);(iv)respiratory function (dyspnea, orthopnea and respiratory insufficiency).^[35]^

Each item within a domain is attributed a score of 0 (complete loss of function) to 4 (normal), yielding a maximum score of 48 when the function is preserved. The ALSFRS-R will be measured at screening, baseline, week 12, 24, 36, and 40.

### Secondary outcome measures

2.3

The secondary outcome measures will be measured at screening, baseline, week 12, 24, 36 and 40. The secondary endpoints will include measures of efficacy and safety.

1.SurvivalSurvival will be defined from symptom onset to death of patients or tracheostomy insertion, whichever occurs first and will be measured in months.2.Lower motor neuron functionLower motor neuron function will be assessed by clinical and neurophysiological biomarkers and will included muscle strength and motor amplitudes.**-Muscle strength**(a) *Medical Research Council score*: Clinical assessment of muscle strength will be made by the Medical Research Council (MRC) score. The MRC score is a standard clinical score used in clinical practice and will be performed by the neurologist at each site. This score assesses muscle strength on a 5-point score as follows:5 = Normal strength.4 = Active movement against gravity and resistance.3 = Weak contraction against gravity.2 = Active movement with gravity eliminated.1 = Minimal contraction.0 = Complete paralysis.The following movements will be assessed in each patient:*-Upper limbs*: Shoulder abduction, elbow flexion, elbow extension, wrist extension, finger extension, finger abduction, and thumb abduction on both sides. The total score when strength normal in the upper limbs will be 70.*-Lower limbs*: Hip flexion, abduction, adduction and extension, knee flexion and extension, and ankle dorsiflexion and plantarflexion. The total score when strength is normal in the lower limbs will be 80. The upper and lower limb MRC scores will be combined yielding a maximum score of 150 (0 severe weakness to 150 normal strength).(b) *Hand dynamometry*: Muscle strength will also be assessed by hand-held dynamometry (JAMAR PLUS, Patterson Medical, Warrenville, IL). A spring-loaded device that “breaks” at pre-set forces will be used to assess readings obtained by hand-held dynamometry throughout the study. Wherever possible, the same rater will be used at each site for each assessment. Grip strength dynamometry for both hands will be acquired, and the mean force in kilograms will be calculated. Measures will be obtained from each hand in triplicate-*Neurophysiological testing:* The degree of lower motor neuron loss will be determined neurophysiological testing performed on nerve conduction study machines (Nicolet EDX, System, Natus, Middleton, WI). The following parameters will be recorded from the intrinsic hand muscles on both sides.(a) *Neurophysiological Index (NPI)*: This is an established measure of lower motor neuron dysfunction in ALS.^[36]^ The NPI will be calculated from by stimulating the median nerve at the wrist and recording the motor response from the abductor pollicis brevis muscle using the following formula: 

Where CMAP is the compound muscle action potential, DML is distal motor latency and F-wave frequency is the number of F-wave that occur with 10 consecutive suprathreshold stimulations.(b) *Split Hand Index (SI)*: The split hand index as an objective biomarker of the split hand phenomenon, an important clinical feature of ALS.^[37–39]^ The SI will be calculated as follows: 

3.Respiratory functionRespiratory function will be assessed by using specific respiratory function tests.-*Forced vital capacity (FVC)*: Forced expiratory volume (FEV) measures how much air a person can exhale during a forced breath. The amount of air exhaled may be measured during the first (FEV1), second (FEV2), or third seconds (FEV3) of the forced breath. Forced vital capacity (FVC) is the total amount of air exhaled during the FEV test. The definition of FVC is therefore, the amount of air which can be forcibly exhaled from the lungs after taking the deepest breath possible. For measuring FVC the patient will be instructed to inhale deeply and exhales completely while in a standing position. Results of the test will be recorded and analyzed by the spirometry machine (Welch-Allyn) and interpreted by the PI. Three trials will be performed and the best FVC result (% of predicted) will be recorded.*-Sniff nasal inspiratory pressure (SNIP)*: The SNIP is the measurement of pressure through an occluded nostril during sniffs performed through the contralateral nostril. It is an accurate and non-invasive approximation of oesophageal pressure swing during sniff manoeuvres. Respiratory strength is assessed by measuring the maximal inspiratory pressure (MIP or PI_max_) and the maximal expiratory pressure (MEP or PE_max_). The MIP reflects the strength of the diaphragm as well as other inspiratory and expiratory muscles.4.Urinary neurotrophin receptor P75 levelThe urinary neurotrophin receptor p75 is a biomarker of neurodegeneration measured by an enzyme-linked immunosorbent assay (ELISA).^[40]^ Specifically, the ELISA test measures the extracellular portion of the neurotrophin receptor p75 that is cleaved from neurons in ALS. Neurotrophin receptor p75 is increased in serum, CSF and urine of ALS patients, although urinary measures are preferable. With disease progression in ALS, there is an increase in neurotrophic p75 levels.^[41,42]^Urinary neurotrophic receptor p75 levels will be measured according to the following protocol:The test will be performed on diluted urine and will be performed in triplicate in 4 separate assays. The mean value is calculated from the 12 measurements.Urinary dilution is accounted for by correcting with creatinine and the level of p75 (ng) will be provided per mg of creatinine.A mid-stream urine sample will be collected into a sterile urine container.The urine samples will undergo urinalysis (SIEMENS Multistix 10 SG) and samples with abnormal readings (high glucose, pH > 8, positive for leucocytes or blood) will be discarded. Eligible urine samples 10–50 mL) will be centrifuged at 2000 g (4°C) for 5 minutes. A 1 mL aliquot will be collected, placed in secure tube, labeled and stored at −80°C within 4 hours of collection) until transported to the ALS Biomarker Centre at Flinders University for analysis.5.ALS Specific Quality of Life Revised (ALSSQOL-R)The ALS Quality of Life Revised is a validated questionnaire that will be used to assess the impact of tecfidera on the patients quality of life.^[43]^ The ALSSQOL-R is a 50-item disease-specific questionnaire covering multiple domains. Each question is scored from 0 (not at all) to 10 (very much) yielding a total score range from 0 to 500. The questionnaire can be completed by most ALS patients in approximately 15 to 20 minutes.6.Assessment of SafetyThe Investigators and study site staff will be responsible for documentation of events meeting the definition of an adverse event (AE) or serious adverse event (SAE). Adverse events will be defined any unfavorable and unintended consequence (including an abnormal laboratory finding), symptom, or disease (new or exacerbated) temporally associated with the use of tecfidera, whether or not considered related to the medicinal product. Disease progression of ALS will not be considered an AE. The potential AEs related to tecfidera are highlighted in Table 1.
